### Adverse Events

The research team will immediately contact the Ethics Review Committee at the Keio University School of Medicine if the participants report any serious adverse events. Serious adverse events are defined as follows: (1) death by suicide, (2) death by nonsuicide, (3) a suicide attempt (self-injurious behavior that admits a suicide attempt), (4) an event that may lead to death, (5) psychiatric hospitalization, (6) general hospitalization due to an adverse event, (7) disability leading to inactivity due to an adverse event, or (8) any events judged to be medically serious based on the Japanese version of Common Terminology Criteria for Adverse Events v3.0 by the Japan Clinical Oncology Group/the Japan Society of Clinical Oncology [66]. Participants are asked to report any adverse events at the end of each session.

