**Figure 1 figure1:**
[figure not shown]
Flowchart of the study. bMBCT consists of four 1.5-hour-long sessions (only session 1 lasts for 2 hours). The follow-up session lasts for 1 hour and consists of a short meditation, experience sharing, and a question-and-answer session. bMBCT: brief version of mindfulness-based cognitive therapy; RCT: randomized controlled trial.

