### Interventions

#### Brief Mindfulness-Based Cognitive Therapy

The included participants were offered a bMBCT program, which is a modified version of the original MBCT developed by Segal et al [45]. The modifications followed Crane et al’s [1] specifications of “warp” (essential ingredients) and “weft” (flexible ingredients) of MBPs. To retain the essential ingredients of MBPs, we included practicing all mindful meditations except mindful movement and walking meditation (provided as homework via a delivery instruction movie). In contrast, considering the difference in the delivery setting (clinical setting vs workplace) and the target population (ie, patients with depression vs healthy individuals), some modifications were made. The first is the structure of the program. With the aim of improving accessibility to the program in the workplace, the duration of each session was shortened (from 2 hours to 1.5 hours), except session 1, and the total number of sessions was reduced (from 8 sessions to 4 sessions). To reflect the difference in the target population, the lecture relevant to depression was deleted, and activity records (ie, pleasant, unpleasant, appreciation events, and nourishing and depriving activities) were introduced to enhance the improvement of participants’ well-being. The specific program contents are listed in Table 1. In the program, participants learned both cognitive approaches and mindfulness practices (eg, raisin exercise, body scan, sitting meditation, exploring difficulty, and 3-step breathing space). The participants were asked to practice meditation daily for approximately 20 minutes by listening to the pre-recorded meditation guide audios and record some activities as homework (theme depends on the session). Monthly follow-up sessions (lasts for 1 hour) will be provided to the participants for 6 months. No regular homework will be assigned during the follow-up period. During the follow-up period, the participants can access the mindfulness website developed by the research team from a smartphone or a personal computer (PC) and easily stream/download the meditation instructions.

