### Control Group

Participants in the control group will wait until the intervention group has completed the intervention. During this waiting period, they have been requested not to attend other mindfulness or meditation activities. After the waiting period is completed (ie, 7 months after allocation), the participants in the control group will be offered the same bMBCT but without monthly follow-up sessions.

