### Limitations

This study has the following limitations. First, as all measures assessed are in self-report format, uncertainty regarding objectivity remains. Second, since we do not have an active control group (we set the waitlist as the control group), we cannot detect the effects that are specifically attributable to bMBCT. However, considering that the main objective of this study is to investigate the effectiveness of augmenting typical daily life with bMBCT rather than to assess the efficacy of bMBCT, we considered the research design to be acceptable for that purpose. Third, although we encourage the participants to report any serious adverse events at the end of each session, we will not assess mild-to-moderate adverse events. Therefore, the adverse events caused by this intervention might be underestimated. Despite the aforementioned limitations, we believe that this study will provide valuable information for future clinical trials in this field.

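### The only stated prompt for adverse events comes at the end of sessions, so the waitlist arm is never prompted during the randomised comparison; the article also contradicts itself on which events are collected

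*Protocol article*

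**What the plan says.** In the protocol article, the Adverse Events section has serious events referred to the ethics committee when participants report them. It then gives one way of asking: "Participants are asked to report any adverse events at the end of each session".

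The Limitations section describes the scope differently: "although we encourage the participants to report any serious adverse events at the end of each session, we will not assess mild-to-moderate adverse events". It adds that "the adverse events caused by this intervention might be underestimated".

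The arms have very different session schedules. Figure 1 and the section on bMBCT give four programme sessions. After these, "Monthly follow-up sessions (lasts for 1 hour) will be provided to the participants for 6 months". For the other arm, the Control Group section says "Participants in the control group will wait until the intervention group has completed the intervention". Those participants are offered bMBCT 7 months after allocation, without the monthly follow-ups.

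Table 2, which covers all participants, has no row for adverse events. It does have a row for health service use, at screening, week 4, 3 months and 6 months. Table 3, which covers the waitlist arm once its waiting period is over, has no adverse-event row either.

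**The concern.** Counts of harms can be compared between arms only if events are looked for in the same way in both. Here the stated prompt is attached to the intervention itself. One arm is asked repeatedly and the other is not asked at all until the randomised comparison is over. Within the bMBCT arm, someone who stays away, possibly because of an event, is not asked on that occasion.

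The limitation that the authors disclose is that events may be under-counted because milder ones are not assessed. It does not mention the difference between arms or the loss of non-attenders.

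The contradiction on scope adds to this. A reader cannot tell whether a count of, say, transient distress after meditation would be a complete collection, a partial one, or outside the plan. The matter is not remote from the trial's purpose: the Discussion's Summary section itself says that misuse of such programmes could be bad for employees' health.

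**Working it through.** The article states no figure for harms, so there is none to reproduce. The check is a count of prompts, an illustration of what unequal prompting does, and a comparison of two sections.

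**1. Prompts per participant during the randomised comparison**

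| Source of prompt | bMBCT | Waitlist |
|---|---|---|
| Programme sessions (Figure 1) | 4 | 0 |
| Monthly follow-ups over 6 months (section on bMBCT) | 6 | 0 |
| Adverse-event item at scheduled assessments (Table 2) | none listed | none listed |
| Total | 4 + 6 = 10 | 0 |

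Ten is a maximum, reached only by someone who attends every session. The open-ended questions under Homework Engagement/Qualitative Data are also asked at the end of sessions, so they do not fill the gap.

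**2. Effect on recorded counts (illustration)**

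Let n be the number per arm, p the true proportion with an event, and c the proportion of events captured. Expected recorded events = n × p × c. Take n = 220 / 2 = 110, from the maximum sample size and 1:1 allocation. The values of p and c are assumptions; the article gives none.

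Equal true harm, full capture in bMBCT (c = 1), and waitlist capture of 0 to 0.5 through unprompted reports:

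| True p, both arms | bMBCT: 110 × p × 1 | Waitlist: 110 × p × (0 to 0.5) |
|---|---|---|
| 5% | 5.5 | 0 to 2.75 |
| 10% | 11 | 0 to 5.5 |
| 20% | 22 | 0 to 11 |

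Equal harm would appear as an excess on bMBCT.

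Now suppose that the truth is 20% on bMBCT and 10% on waitlist, a true difference of 22 − 11 = 11 events:

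- Capture 1 on bMBCT and 0 on waitlist: 22 − 0 = 22 recorded. The excess is overstated.
- Capture 0.5 in both arms, with bMBCT capture lowered because affected people skip sessions: 11 − 5.5 = 5.5 recorded. The excess is understated.

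The sign of the error depends on two capture rates that the plan neither controls nor measures.

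**3. The two statements of scope**

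- Adverse Events (Methods): participants are asked about all adverse events, with no limit on severity.
- Limitations (Discussion): "although we encourage the participants to report any serious adverse events at the end of each session", and then "we will not assess mild-to-moderate adverse events".

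Both describe the same occasion, the end of a session. If all events are asked about, the milder ones are collected in some form. If milder ones are not assessed, the Methods sentence is wrong or incomplete. A difference in grading or follow-up might explain the two statements, but the article does not say so.

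**The case against.** The strongest reply is that the article does not call session-end asking the only route. The referral rule for serious events applies to any participant who reports one, in either arm and whether or not they attend. The list of serious events includes deaths, which no participant can report at a session, so some other route was presumably intended. A condensed article may leave that route to the full protocol. This stands as far as it goes: the finding concerns the only prompt that the article states, and unprompted reports from waitlist participants are not ruled out.

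The health service use item is collected in both arms and is not tied to sessions, so it might reveal some admissions. That also stands, although the item is not described as adverse-event collection.

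Harms are neither a primary nor a secondary outcome, and the Statistical Analysis section plans no between-arm test of them. The authors' own answer to the worry about misuse is to measure stress and well-being in both arms. Those scales are collected symmetrically, but they do not record events such as a hospitalisation.

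Three stronger readings are tempting, and the article does not support them:

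- **Any harms table would show events in one arm only, or no comparison would be possible.** Unprompted reports and the health service use item could bring up waitlist events. The supported statement is that a comparison would be biased.
- **A quarter of the bMBCT arm would fall out of ascertainment.** The 25% in the Sample Size section is a dropout allowance for the whole trial. It is not a rate of missing sessions, and people who leave may have been asked at sessions they attended.
- **The arrangement hides harm from the intervention.** Prompting only the bMBCT arm pushes the other way, towards making bMBCT look worse.

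None of these replies removes the imbalance of up to 10 prompts against none, or the conflict between the two sections.

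**Conclusion.** The concern holds in a limited form. On the article's stated rule, the bMBCT arm is prompted for adverse events on up to 10 occasions in the randomised comparison and the waitlist arm on none; bMBCT participants are not prompted at sessions they skip. Any between-arm description of harms drawn from these reports would be biased, in a net direction that cannot be determined. Serious events in waitlist participants and non-attenders depend on someone volunteering them or on incidental capture. The disclosed limitation does not cover this. The contradiction on which events are collected is plain from the text.

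This assumes that the article states every prompt in use. If the full protocol has a prompt common to both arms, what remains is to state it in the article and to resolve the contradiction. The event counts in the illustration depend on assumed event and capture proportions; the count of prompts does not. The primary analysis is unaffected.

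**What to change.** 1. Add a short adverse-event item, covering any new or worsened health event and any hospitalisation, to the electronic questionnaires that both arms already complete at 4 weeks, 3 months and 6 months. Ask it whether or not the participant attends sessions.
2. Make that item the main source for any between-arm summary of harms. Report session-end events separately, as a bMBCT-arm description.
3. State the date on which the item was introduced, and which assessments came before it. It cannot be the sole basis for comparison, because 104 participants had already been enrolled by October 2021.
4. Reconcile the Adverse Events and Limitations sections on which events are collected, and extend the stated limitation to the difference in prompting between arms.

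The cost is a questionnaire change with an ethics notification, a little more reporting, and someone to review the responses as they arrive. No extra visits are needed. Two gaps remain: there will be no such data for assessments completed before the item was added, and people who stop answering questionnaires will still be missed.

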### Ethics Approval

The authors confirmed that all procedures complied with the ethical standards of the relevant national and institutional committees on human experimentation and with the tenets of the 1975 Declaration of Helsinki, revised in 2008. All procedures involving human participants and patients were approved by the Ethics Review Committee of the Keio University School of Medicine (Reference 2021-0101). All included participants provided informed consent after all procedures were explained in detail. They were allowed to withdraw their consent at any time without any negative consequences.

### Dissemination

We expect the results of our research to be presented at conferences and published as papers in academic journals. The results of this research will adhere to the Consolidated Standards of Reporting Trials (CONSORT) statement.

## Results

We started recruiting participants in August 2021, and the intervention began in October 2021. A total of 104 participants have been enrolled in the study as of October 2021. The intervention is scheduled to be completed in December 2023. Data collection will be completed by the end of January 2024.

## Discussion

### Summary

The aim of this study is to evaluate the effectiveness and cost-effectiveness of bMBCT in the workplace, especially for productivity. This study is valuable because it will fill certain gaps in the existing MBCT research. First, previous studies have revealed that the effectiveness of MBPs for physical and psychological indicators (eg, stress, burnout, and sleep well-being,) is promising; however, its effects on productivity are still unclear. This study is expected to clarify this important aspect of the use of MBPs in the workplace. Second, as the participants of this study are being recruited from 3 companies in different industries (security, education, and processed foods), the generalizability of the study findings will be enhanced because the cohorts of previous studies were recruited from a single company. Third, this study will focus on the evaluation of the effectiveness of online bMBCT in the workplace. Since the accumulated evidence on the effect of online bMBCT is still insufficient, the results of this study will advance the understanding of the use and effect of online bMBCT in the workplace. This is particularly important in the current scenario where many employees are forced to work from home. Furthermore, we will compare the effectiveness of bMBCT with follow-up and bMBCT without follow-up. The participants in the waitlist control group will receive bMBCT without follow-up once the waiting period is completed. Although this is not a direct RCT-based comparison, we can preliminarily evaluate the differences between the effect of bMBCT with and bMBCT without follow-up. Finally, we included a scale for the assessment of an organization’s culture. Although previous studies have revealed that an individual’s productivity is affected by individual factors and their organization’s culture, such as team psychological safety, the interaction between individual and organizational factors has not been assessed to date. In the multivariate analysis, we plan to investigate the effect of differences in an organization’s culture on the study outcomes. We are aware that focusing on productivity may possibly induce the increase of the “craving mind” of the participants, which is contrary to the purpose of MBPs. Such misuse of MBPs could have a negative impact on employees’ health and well-being. Therefore, we will also assess these outcomes as well as productivity in order to evaluate the suitability of our MBP.

### Limitations

This study has the following limitations. First, as all measures assessed are in self-report format, uncertainty regarding objectivity remains. Second, since we do not have an active control group (we set the waitlist as the control group), we cannot detect the effects that are specifically attributable to bMBCT. However, considering that the main objective of this study is to investigate the effectiveness of augmenting typical daily life with bMBCT rather than to assess the efficacy of bMBCT, we considered the research design to be acceptable for that purpose. Third, although we encourage the participants to report any serious adverse events at the end of each session, we will not assess mild-to-moderate adverse events. Therefore, the adverse events caused by this intervention might be underestimated. Despite the aforementioned limitations, we believe that this study will provide valuable information for future clinical trials in this field.

### Conclusion

This study has the potential to provide new data on the relationship between MBPs and occupational health and productivity.

## Abbreviations

bMBCT: brief mindfulness-based cognitive therapy
CEQ: Credibility/Expectancy Questionnaire
EQ: Experiences Questionnaire
FFMQ: Five Facet Mindfulness Questionnaire
FS: Flourishing Scale
ICECAP-A: Investigating Choice Experiments Capability Measure for Adults
MBP: mindfulness-based program
MMRM: mixed model repeated measurement
PSS: Perceived Stress Scale
RCT: randomized controlled trial
SPANE: Scale of Positive and Negative Experience
SWLS: Satisfaction With Life Scale
TPS: Team Psychological Safety
UWEC-9: 9-item Utrecht Work Engagement Scale
WHO-HPQ: World Health Organization Heath and Work Performance Questionnaire
